### Relevant concomitant care permitted or prohibited during the trial {11d}

Caregivers will be ineligible for participation if they are engaged in regular individual psychotherapeutic support that they are unable or unwilling to put on hold for the course of the intervention. The use of psychotropic medications while engaging in the trial is permitted.

### Provisions for posttrial care {30}

There are no provisions for posttrial care. However, should a participant specifically request referrals for ongoing support after completion of the trial, the study team will provide appropriate resources.

### Outcomes {12}

As outlined in the participant timeline, assessments will occur at four time points: baseline (T1), posttreatment (T2), and 6-month (T3) and 12-month (T4) follow-up (Fig. 1). Section “Plans for assessment and collection of outcomes {18a}” includes detailed descriptions of outcome measures. The SPIRIT figure for the trial is shown in Fig. 2.

**Fig. 1 Fig1:**
[figure not shown]
Study timeline

**Fig. 2 Fig2:**
[figure not shown]
SPIRIT figure. Participant timeline: schedule of enrollment, interventions, and assessments. ^a^This measure is only completed for the time points after which a participant has become bereaved, if applicable. These questionnaires are not completed by participants who are not bereaved

All primary and secondary outcome measures for Aim 1 are continuous variables that will be assessed at all four time points (T1, T2, T3, and T4). For each outcome measure, our main parameter of interest is the model-estimated difference in mean change scores from T1 to T2 between the MCP-C and SP-C treatment arms (see section {20a} for model details). For each outcome, as exploratory parameters, we will also examine the model-estimated differences in mean change scores from T1 to T3 and from T1 to T4 between the MCP-C and SP-C treatment arms. The two co-primary outcome measures are sense of meaning in life, as measured by the LAP-R PMI, and spiritual well-being, as measured by the FACIT SWBS. Secondary outcome measures include anxiety (HADS-A subscale) and depression (HADS-D subscale), sense of meaning and purpose in caregiving (ATCS total score), benefit finding (BFS), caregiver burden (CRA), and social support (FSSQ).

For Aim 2, we will evaluate the extent to which changes in LAP-R PMI scores from T1 to T2 mediate the model-estimated differences in mean change scores from T1 to T3 of three outcome measures (BFS, HADS-A, and HADS-D) between the MCP-C and SP-C treatment arms.

The Aim 3 bereavement outcomes are divided into pre-loss and post-loss outcome measures. The pre-loss measures will be administered at T1 to all caregivers and at T2, T3, and T4 for caregivers who remain non-bereaved at those time points. The post-loss measures will be administered at T2, T3, and T4 to caregivers who are bereaved at those time points. Because of the reduced sample sizes for the analyses of the pre-loss and post-loss outcomes, the Aim 3 outcomes are exploratory. The pre-loss outcomes are preparedness for patient death (three-category response to single item with values “not at all,” “somewhat,” and “very”), pre-loss grief intensity (PG-12-R score), and risk for bereavement mental health challenges (BRISQ-P score). For preparedness for patient death, the parameters of interest are differences between the two treatment arms in the model-estimated proportions of non-bereaved caregivers responding “somewhat” or “very” at T4. For the PG-12-R and BRISQ-P, our main parameter of interest is the model-estimated difference in mean change scores from T1 to T2 between the two treatment arms among non-bereaved caregivers. The post-loss outcomes include two dichotomous (yes/no) outcomes (the presence of regret, unfinished business) and the continuous outcomes of post-loss grief intensity (PG-13-R) and risk for post-loss bereavement mental health challenges (BRISQ-B). The parameters of interest for the presence of regret and unfinished business are the differences between the treatment arms in the model-estimated proportions of bereaved caregivers responding “yes” to these items at T4. For the PG-13-R and BRISQ-B, our main parameter of interest is the model-estimated difference in mean scores at T4 between the two treatment arms among bereaved caregivers.

### Participant timeline {13}

Potential participants will be screened for eligibility (approximately 5 min) and will meet criteria if they report distress ≥ 4 on the distress thermometer and indicate that the distress is related to caregiving. If interested, participants will complete informed consent procedures and will be offered to immediately complete baseline (T1) assessments. Participants will have up to 45 days (consent expiration) to complete baseline assessments. Once baseline assessments are complete, they will be randomized to either MCP-C or SP-C and assigned to a therapist for seven individual sessions that will be completed over Webex. Participants will have up to 14 weeks to complete all seven sessions. After intervention completion, participants will complete follow-up assessments immediately posttreatment (T2, +2 weeks), 6-month follow-up (T3, ±4 weeks), and 12-month follow-up (T4, ±8 weeks). See Fig. 1 for the full study timeline.

### Sample size {14}

Participants will be 200 caregivers recruited across study sites and the community, with 100 caregivers randomized to each study arm (MCP-C vs. SP-C). The sample size was chosen to provide 80% power to detect reasonable treatment effect sizes for our two primary endpoints while maintaining the type 1 error rate at *α*= 0.05 for these comparisons. Using methods relevant to clinical trials with repeated measures [31], we calculated the smallest effect size that we will be able to detect for the immediate posttreatment coefficient of the time-by-arm interaction term in our linear mixed model analysis of one of the two primary outcome measures (LAP-R PMI). Given the sample size (*N* = 200), we will be able to detect a standardized mean difference treatment effect size between the two study arms of 0.48 standard deviations. This calculation assumed a correlation between baseline and follow-up measures of 0.5, 20% attrition by the posttreatment assessment, a two-sided significance test, and a type 1 error of 0.025 (0.05 overall for both primary endpoints).

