#### Aim 1: Analytic plan

The primary and secondary outcome measures for Aim 1 are all continuous variables assessed repeatedly over the four time points: baseline (T1), immediately posttreatment (T2), 6-month follow-up (T3), and 12-month follow-up (T4). The co-primary efficacy endpoints for Aim 1 are the LAP-R PMI and FACIT SWBS at the immediately posttreatment assessment (T2). We will consider MCP-C efficacious if MCP-C participants have significantly greater improvements than SP-C participants in LAP-R PMI or FACIT SWBS scores at T2 at the *p*< 0.025 statistical significance threshold in the analysis described below. We will analyze each continuous primary and secondary outcome measure by using constrained linear mixed model (cLMM) regression [52–54]. This statistical method accounts for within-subject correlations due to repeated measurement of participants and, under the reasonable missing at random (MAR) assumption, allows unbiased estimation of between-group differences without excluding participants with missing follow-up data. Each of these outcome measures will be analyzed using a separate cLMM regression with random intercept that will model the baseline and repeated follow-up scores (dependent variable) as a function of time (categorical) and the time-by-arm interaction, controlling for the randomization stratification variable (study site). The cLMM method will also constrain the two study arms to have a common baseline mean on the outcome measure to reflect the pre-randomization nature of the baseline assessment (T1) [52]. All randomized participants will have, at a minimum, the baseline (T1) primary outcome assessments and will be included in the cLMM per the intention-to-treat principle. In the cLMM parameterization, the coefficients for the time-by-arm interaction are equivalent to the differences between arms in outcome measure score changes from baseline to the post-baseline time points, and they will be calculated with 95% confidence intervals (CIs). For each co-primary endpoint (LAP-R PMI and FACIT SWBS), we will conclude that MCP-C participants had significantly larger improvements in the endpoint at T2 compared to SP-C if the time-by-arm interaction coefficient for T2 is significantly larger than 0 at the *p* < 0.025 level. The secondary outcome measures will be compared between study arms using similar cLMM analyses. However, we will assess estimated treatment effects at each timepoint using 95% CIs instead of *p*-values.

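### The stated detectable effect of 0.48 SD does not belong to the planned constrained mixed model, which on the same inputs detects about 0.42 to 0.43 SD at 80% power

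*Protocol article*

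**What the plan says.** The Sample size section sets 100 caregivers per arm and gives the aim of the calculation: "The sample size was chosen to provide 80% power to detect reasonable treatment effect sizes for our two primary endpoints". The target quantity is "the immediate posttreatment coefficient of the time-by-arm interaction term in our linear mixed model analysis", worked out for the LAP-R PMI, and the result is that "we will be able to detect a standardized mean difference treatment effect size between the two study arms of 0.48 standard deviations". The section introduces this as the smallest effect that can be detected.

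The inputs are listed. "This calculation assumed a correlation between baseline and follow-up measures of 0.5", together with "20% attrition by the posttreatment assessment", a two-sided test, and a type 1 error of 0.025 for each of the two co-primary endpoints. No design effect is listed. The method is given by a citation and the formula is not shown.

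The Aim 1 analytic plan then specifies the model: a random-intercept linear mixed model with categorical time and a time-by-arm interaction. "The cLMM method will also constrain the two study arms to have a common baseline mean on the outcome measure". Participants without follow-up data stay in the model through their baseline score.

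**The concern.** The two sections describe the same coefficient, the T2 time-by-arm term, but the number in one does not follow from the model in the other. Forcing a common baseline mean gives the T2 contrast the precision of a baseline-adjusted comparison. Without the constraint, the contrast is a difference in change scores and carries the noise of two separately estimated baseline means. At a correlation of 0.5 the two differ by more than rounding.

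This is the plan's only power statement for the co-primary endpoints. If 0.48 SD is not the 80%-power effect of the planned analysis, true effects between about 0.42 and 0.48 SD are presented as falling short of 80% power when, on the stated assumptions, they do not.

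**Working it through.** **Inputs, all from the Sample size section:** 100 randomized per arm; 20% attrition, so 80 per arm with T2 data; correlation ρ = 0.5; two-sided alpha 0.025; power 80%. The outcome SD is set to 1 at both times and participants are treated as independent.

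**Multiplier:** z(0.9875) + z(0.80) = 2.2414 + 0.8416 = 3.083. The detectable effect is 3.083 × SE of the T2 time-by-arm coefficient.

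**Step 1. Reproducing the stated figure (separate baseline means, all available data).**
- Var = 2[(1 − ρ²)/80 + ρ²/100 + 1/100 − 2ρ/100]
- = 2[0.75/80 + 0.25/100 + 0.01 − 0.01] = 2[0.009375 + 0.0025] = 0.02375
- SE = 0.1541; detectable effect = 3.083 × 0.1541 = 0.475 (0.478 to 0.479 with the t distribution)
- This rounds to 0.48. Power at 0.48 SD is 0.809.

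**Step 2. The planned model (common baseline mean).**
- Var = 2(1 − ρ²)/80 = 2 × 0.75/80 = 0.01875
- SE = 0.1369; detectable effect = 3.083 × 0.1369 = 0.422 (0.425 to 0.426 with the t distribution)
- Power at 0.48 SD = Φ(0.48/0.1369 − 2.2414) = Φ(1.264) = 0.897

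**Step 3. Robustness.** A generalized least squares calculation gives both results. Adding T3 and T4, later monotone dropout or an AR(1) correlation leaves them unchanged. A simulation of 40,000 trials gives 0.474 (separate) and 0.423 (common).

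**Step 4. Other routes to 0.48.**

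| Calculation | Detectable effect | Fits the stated inputs and the planned model? |
|---|---|---|
| Unadjusted or change score, 80 per arm: 3.083 × √(2/80) | 0.4875 | No: rounds to 0.49 and ignores the constraint |
| Same, attrition taken as 100/1.2 ≈ 83 per arm: 3.083 × √(2/83) | 0.479 | No: ignores the constraint |
| Constrained model at 90% power | 0.482 | No: the section states 80% |
| Constrained model with a variance inflation of (0.48/0.422)² ≈ 1.29 | 0.48 | Only with a design effect the section does not mention |
| Constrained model, effect in residual SD units: 0.422/√0.75 | 0.49 | No |

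The choice between raw-score and change-score SD does not explain the gap: at ρ = 0.5 the change-score SD is √[2(1 − 0.5)] = 1, the same as the raw SD. None of these makes 0.48 the 80%-power effect of the constrained model on the inputs given.

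**The case against.** The strongest reply is that the error is on the safe side and changes no decision. This stands. The sample size is fixed, the trial can detect 0.48 SD on the stated assumptions, and its power there is about 90% instead of 80%. Only the claim that 0.48 is the smallest such effect fails. It is also true that a null result will be judged mainly from the confidence interval of the fitted model, not from a planning figure, so the harm to interpretation is modest.

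A second reply is that the calculation method is only cited, so the model used cannot be known. This also stands, and it limits what can be said. A reader might infer from the match at 0.475 that the planners used separate baseline means. The documents do not establish this, because a change-score calculation with 83 per arm gives 0.479. What can be shown is that the stated result does not fit the planned model. Nor is this a matter of detail left to a fuller document: the model, coefficient, inputs and result are all in the article, and they do not agree.

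A third reply is that 0.48 may contain a margin for therapist clustering. The section lists its assumptions and names no such margin. If one was intended, it should be stated.

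**Conclusion.** The point holds as a mismatch between the power statement and the planned analysis. On the plan's own inputs the constrained model detects about 0.42 SD at 80% power (0.43 with the t distribution), against the stated 0.48, and its power at 0.48 SD is about 90%. This assumes equal SDs at T1 and T2, a correlation of exactly 0.5, 80 per arm at T2, and independent participants.

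Three stronger readings are not supported. The trial is not shown to be too small: under independence the error runs the other way. It is not shown to be too large either. The constrained model would need only about 200 × (0.422/0.48)² ≈ 155 randomized for 0.48 SD at 80% power, but that leaves out therapist clustering, and the article does not justify 0.48 as a target that would warrant a smaller trial. Finally, a reader might conclude that clustering pulls power at 0.48 SD below 80%. Each condition does have its own therapists, so clustering would work against the margin found here. But the article gives neither the number of therapists nor an intraclass correlation, so its size cannot be derived from the document.

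**What to change.** Keep N = 200. In the Sample size section, replace the current figure with the one for the planned model: a detectable effect of about 0.42 to 0.43 SD of the raw score at 80% power, or equivalently about 90% power at 0.48 SD. Say that it relies on the common baseline mean and assumes no therapist clustering. If 0.48 was meant to include a design effect, or to describe a model without the baseline constraint, state that design effect or model instead. The cost is a sentence or two of text, with no change to recruitment, analysis or decision rule.

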### Recruitment {15}

To maximize recruitment and retention, this study employs a multi-site design where participants will be recruited from outpatient clinics in various departments at MSK and SCCC. At both sites, we will employ three recruitment strategies. Flyers will be posted (digitally or using paper with the clinic’s permission) in clinics at MSK and SCCC. Study contact information will be provided on each flyer where caregivers can reach out to learn more about the study. Participants will also be recruited through patient appointments. Physicians will either directly provide caregivers with the contact information of the study team, or the study team will approach caregivers during or after patients’ next clinic appointment and introduce the study. Third, if clinicians who are aware of the study receive an inquiry from a caregiver about supportive services, they will provide their information to the study team who will subsequently send a study invitation letter to the caregiver via email. The study team will then make 3–5 follow-up calls/emails to discuss interest and participation with the caregiver.

Recruitment from community partners will occur through listservs and social media channels (e.g., Twitter/X, Facebook) of both the American Cancer Society and the National Alliance for Caregiving in states where MCP-C and SP-C supervisors are licensed (New York, New Jersey, Florida, and Connecticut). These advertisements will include study team information and will direct potential participants to contact the study team by email. Caregivers from New York and New Jersey will be enrolled at MSK, and those from Florida and Connecticut will be enrolled at SCCC. During the initial approach and informed consent conversation, study team members will ensure that participants reside in a state where the MCP-C and SP-C supervisors are licensed and may be asked to provide certain health information that is necessary for the recruitment and enrollment process.

## Assignment of interventions: allocation

### Sequence generation {16a}

Participants will be randomized to either MCP-C or SP-C using MSK’s clinical research database, a secure computer system that ensures allocation concealment. Randomization will be 1:1 (MCP-C:SP-C) stratified by study site (MSK, SCCC, community/MSK, and community/SCCC) using randomly permuted blocks of random length. Given the clear focus of MCP-C versus SP-C on unique meaning-focused themes, participants and their study interventionists will not be blinded to intervention assignment.

### Concealment mechanism {16b}

#### Implementation {16c}

Participants will be randomized 1:1, stratified by study site, to MCP-C or SP-C using MSK’s clinical research database, a secure computer system that generates the randomization sequence and ensures allocation concealment by using randomly permuted blocks of random length to allocate participants to study arm. Participants will be enrolled by a consenting professional at the corresponding study site, and the clinical research database will assign the intervention arm.

## Assignment of interventions: blinding

### Who will be blinded {17a}

Neither participants nor their study interventionists delivering MCP-C and SP-C will be blinded to intervention assignment due to the clear focus of the MCP-C intervention on meaning and existential content and SP-C on the provision of support. However, the study biostatistician who will conduct the analyses will be blinded.

### Procedure for unblinding if needed {17b}

N/A.

## Data collection and management

### Plans for assessment and collection of outcomes {18a}

Data will be collected via self-report measures using the Research Electronic Data Capture (REDCap), a secure web application for creating and managing online survey databases. The Clinical Research Coordinator (CRC)—who receives training in data quality assurance—will send all study assessments to participants at the appropriate timepoint. Outcomes will be measured at four time points: baseline, directly after informed consent or until consent expiration (i.e., 45 days; T1), immediately post-intervention + 2 weeks (T2), 6-month follow-up ± 4 weeks (T3), and 12-month follow-up ± 8 weeks (T4). This will allow flexibility for study assessment completion and aid caregiver retention throughout the entire study. All data collection forms can be found in the study protocol.

At baseline (T1), participants will complete demographic information (e.g., age, sex, race, ethnicity, income), caregiver characteristics (e.g., relationship to the patient, length of caregiving), and a survey about psychosocial service use, preferences, and perceived barriers, using established questionnaires from our group’s previous studies. Participants will also complete all outcome measures (i.e., sense of meaning in life, spiritual well-being, anxiety and depression, benefit finding, meaning in caregiving, caregiver burden, and social support) at T1. At T2, in addition to study outcome measures, participants will complete the Credibility and Expectancy Questionnaire (CEQ) to assess treatment acceptability and perceived effectiveness. Pre-loss (preparedness for patient death, pre-loss grief intensity, risk for bereavement mental health challenges, engagement in advance care planning) and post-loss (the presence of regret, unfinished business, post-loss grief intensity, risk for post-loss bereavement mental health challenges, and occurrence of advance care planning discussions and goal-concordant care at patients’ end of life) bereavement outcomes will also be explored at all timepoints.

#### Description of study measures

##### Screening and non-outcome measures

Caregiving-related distress: A modified version of the Distress Thermometer (DT) [32] will be used to screen for distress related to caregiving. Participants are asked to rate their distress on a scale of 0–10 (cutoff score ≥ 4) and indicate that their distress is related to caregiving to be eligible for the study. The distress thermometer will be administered at screening only.Treatment acceptability and perceived effectiveness: The Credibility and Expectancy Questionnaire (CEQ) is a 6-item measure of treatment acceptability and perceived effectiveness [33, 34]. This measure has been used extensively in prior research and has strong psychometric properties [34]. The CEQ is administered at T2 only.

##### Primary outcomes

Sense of meaning in life: The Life Attitudes Profile-Revised (LAP-R) [35] is a 48-item measure of meaning in life, with items rated on a 7-point Likert scale from *strongly agree* to *strongly disagree*, with higher scores indicating a stronger presence of that type of meaning. The LAP-R generates two composite scores: the Personal Meaning Index (PMI) and existential transcendence (ET). The LAP-R has demonstrated strong internal consistency in previous research (Cronbach’s α range: 0.77–0.91) [35]. The LAP-R is administered at T1–T4. The LAP-R PMI at T2 is one of our two co-primary outcome measures.Spiritual wellbeing: The FACIT Spiritual Well-Being Scale (SWBS) [36] is a 12-item measure of spiritual well-being measured on a 0 (not at all) to 4 (very much) scale, with higher scores indicating higher spiritual wellbeing. This measure has demonstrated strong internal consistency across all subscales in cancer caregivers (Cronbach’s α range: 0.88–0.93) [26]. The SWBS is administered at T1–T4. The FACIT SWBS at T2 is one of our two co-primary outcome measures.

##### Secondary outcomes

Anxiety and depressive symptoms: The Hospital Anxiety and Depression Scale (HADS) is a 14-item measure of anxiety and depressive symptoms with items rated on a 0 to 3 scale, with higher scores indicating greater symptomatology. Scoring the HADS yields anxiety (HADS-A) and depression (HADS-D) subscale scores, each consisting of seven items. The HADS subscales have demonstrated strong internal consistency in cancer caregiver populations (Cronbach’s α range: 0.82–0.92) [26, 37]. The HADS is administered at T1–T4. Sense of meaning and purpose in caregiving: The Attitudes Toward Caregiving Scale (ATCS) [38] is a 43-item measure rated on a 5-point Likert-type scale that examines the extent to which caregivers find meaning in caregiving. Scores can be summed for a total score in addition to three subscales: loss/powerlessness, provisional meaning, and ultimate meaning, with higher scores indicating higher overall meaning and purpose. The ATCS is administered at T1–T4 in non-bereaved caregivers.Benefit finding: The Benefit Finding Scale (BFS) is a 17-item measure of perceived benefit finding that has been modified for caregiver populations. It has been used in our group’s previous research and has demonstrated strong internal consistency (Cronbach’s α range: 0.91 to 0.95 [39, 40]. The BFS is administered at T1–T4. Caregiver burden: The Caregiver Reaction Assessment (CRA) is a 24-item measure with items scored on a 5-point Likert-type scale [41]. Items are summed for a total score (range: 24–120) across five subscales: self-esteem, family support, impact on finances, schedule, and health. The CRA is a widely used measure of caregiver burden that has demonstrated good internal consistency and construct validity [42]. The CRA is administered at T1–T4 in non-bereaved caregivers.Social support: The Duke-UNC Functional Social Support Questionnaire (FSSQ) is an 8-item measure of perceived social support. Items are summed to a total score ranging from 0 to 40, with higher scores indicating greater perceived social support. The FSSQ has demonstrated strong internal consistency (Cronbach’s α = 0.94) [43]. The FSSQ will be administered at T1–T4.

